**Methods/design:**

This is a multi-centre cluster-randomised controlled trial involving three countries with varying malaria endemicity; low (The Gambia) versus high transmission (Burkina Faso and Benin), and varying degrees of SP resistance (high in Benin and moderate in Gambia and Burkina Faso). CHW and their related catchment population who are randomised into the intervention arm will receive specific training on community-based case management of malaria in pregnancy. All women in both study arms will be enrolled at their first ANC visits in their second trimester where they will receive their first dose of IPTp-SP. Thereafter, CHW in the intervention arm will perform scheduled monthly screening and treatment in the womens homes. At time of delivery, a placental biopsy will be collected from all women to determine placental malaria. At each contact point, filter paper and blood slides will be collected for detection of malaria infection and SP resistance markers.

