#### Intervention communities

CHWs allocated to the intervention arm will follow specific training on community-based case management of malaria, the need for monthly testing of pregnant women using a rapid diagnostic test (RDT), and on issues related to malaria in pregnancy, including the benefit of IPTp-SP and administering SP as early as possible in the second trimester of pregnancy.

The CHWs will continuously identify all pregnant women in their own catchment area, visit eligible women in their home and encourage them to attend the ANC as early as possible in their pregnancy for enrolment. The CHW will check after a week if the ANC was visited. For women who do not attend the ANC, the CHW will further encourage and discuss reasons for non-attendance.Thereafter, at monthly intervals up to the last week of gestation, the CHW will revisit the study participant’s house (Figure 2). The CHW will collect a blood slide and a blood spot on filter paper, perform a RDT and administer a full course of AL to any woman with a positive RDT. In case of treatment, the CHWs will return to assess uptake and compliance by administering a short questionnaire and checking the empty packaging of the treatment at the end of the course.

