#### Control communities

In control communities, CHW will not be trained to administer RDT and AL to pregnant women. The women will be mainly followed through their attendance to the health facilities at the ANC.

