### Clinical data collection and patient treatments

#### At the antenatal clinic

All study participants returning to the ANC for scheduled or unscheduled visits will undergo a health assessment by study staff. In case of suspected malaria (fever, headache, and so forth), a RDT test will be performed and, if positive, AL administered.

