### Analytical plan

Appropriate summary statistics (that is, mean and standard deviation for normally distributed variables and median and inter-quartile range for non-normally distributed variables) will be used to describe the baseline data.

The primary analysis will compare the prevalence of placental malaria (defined as number of positive samples by total number of samples) between the intervention and the control group.

Secondary analysis will compare the following variables between trial arms: (i) mean haemoglobin levels and prevalence of anaemia (haemoglobin <11 g/dL) at delivery, (ii) prevalence of *P. falciparum* peripheral infection (microscopy and PCR) at delivery and during pregnancy, (iii) mean birth weight and proportion of newborns with low birth weight (<2,500 g) between the two trial arms, (iv) level of ANC attendance by village/cluster and coverage of IPTp-SP (defined by number of doses completed during pregnancy), and (v) SP resistance markers profiles.

For the primary and secondary analysis both linear regression (for continuous outcomes such as haemoglobin levels) and logistic regression (for binary outcomes such as placental malaria) will be used to quantify the difference between trial arms. The regression models will allow for the multi-level structure of the data (that is, individuals within villages) using random effects and for all relevant co-variates to be taken into account. Model assumptions will be checked to confirm reliable estimates.

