In this study, it is proposed to add an “extension” strategy to the communities in rural areas to the standard IPTp-SP delivered through the health facilities and thus bring health services closer to where women live. The study will build on the use of CHWs who are already managing malaria cases within the framework of CCMm [18]. At this level, RDTs for the diagnosis of malaria are already being used or their implementation is planned. CCMm supported by RDT is at various stages of implementation; in The Gambia, the National Malaria Control Program is planning to introduce nationwide CCMm supported by RDT; in Burkina Faso, CCMm has been implemented and is currently managed by an international non-government organisation (Plan International) and four local non-government organisations under the supervision of the National Malaria Control Program; in Benin, CCMm is part of the National Malaria Policy, though it still needs to be scaled up nationwide.

The study will extend the CCMm which at present is primarily aimed at children under the age of 5 years to pregnant women. The aim is to improve both IPTp-SP coverage as CHWs encourage women to attend the ANC for the IPTp at the right time, allow systematic screening for malaria infection and provide an opportunity to treat malaria when the prophylactic effect of IPTp-SP has waned. The trial will also investigate the prevalence of SP resistance markers in the positive malaria samples obtained during the study as it could be hypothesized that the beneficial effects of the intervention might be more pronounced in areas with high SP resistance, because women could be more prone to placental malaria when IPTp-SP has a reduced effect and, although not yet observed in West Africa, extremely high levels of SP resistance markers in the parasite population may even lead to adverse effects of SP [34].

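### The between-arm comparison of peripheral infection during pregnancy is confounded by the sampling schedule: monthly home sampling in one arm, mainly clinic-driven sampling in the other

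*Protocol article*

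**What the plan says.** All places are in the protocol article.

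- **The comparison.** Analytical plan, item (ii), sets the prevalence of "peripheral infection (microscopy and PCR) at delivery and during pregnancy" side by side between trial arms. Secondary endpoints lists the same outcome, and Study objectives asks for protective efficacy on maternal peripheral infection. Item (v) of the Analytical plan adds "and (v) SP resistance markers profiles" without a time point.
- **Intervention arm.** Intervention communities: "at monthly intervals up to the last week of gestation, the CHW will revisit the study participant’s house". At each visit, "The CHW will collect a blood slide and a blood spot on filter paper, perform a RDT". The section on CHW home visits states that this monthly testing does not depend on symptoms.
- **Control arm.** Control communities: "The women will be mainly followed through their attendance to the health facilities at the ANC". No scheduled home sampling is described, and Data handling and record keeping confines the monthly CHW form to the intervention arm.
- **When samples are taken.** Abstract, Methods/design: "At each contact point, filter paper and blood slides will be collected for detection of malaria infection and SP resistance markers". At the antenatal clinic: "All study participants returning to the ANC for scheduled or unscheduled visits will undergo a health assessment".
- **Delivery.** At time of delivery for all communities sets the same blood sample for both arms, with staff following up women who deliver at home.
- **SP markers.** The Discussion speaks of the "prevalence of SP resistance markers in the positive malaria samples obtained during the study".

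**The concern.** Samples follow contacts, and contacts differ by arm by design in number, timing and trigger. Home visits in the intervention arm add monthly samples from women who are mostly not seeking care. Control samples come mainly from clinic attendance, some of it prompted by illness. The number of clinic contacts is also open to the intervention, because CHWs urge women to attend and the number of ANC visits is a secondary endpoint.

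A difference between arms in infection during pregnancy could then arise with no effect of the intervention, or a real effect could be hidden or reversed. The result would be reported against a named efficacy objective. The planned models do not remove the problem: the random effects described are for individuals within villages, and adjusting for the number of samples would condition on something the intervention can change.

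**Working it through.** The plan gives no figure for this comparison; its sample size concerns placental malaria only. The documents state neither the number of samples per woman nor the positivity per sample. Both are assumed below and varied. Every scenario has **no true effect** unless stated.

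**1. Counting women ever positive.** With positivity *p* per sample, *n* samples and independence between samples, P(ever positive) = 1 − (1 − *p*)^*n*. Assumed: *p* = 5% to 15%; 5 to 7 samples per intervention woman (monthly visits over the roughly 6 months of follow-up given in Timetable of event); 2 to 3 per control woman.

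| *p* | Samples, control v intervention | Control | Intervention | RR |
|---|---|---|---|---|
| 5% | 2 v 7 | 1 − 0.95² = 9.8% | 1 − 0.95⁷ = 30.2% | 3.09 |
| 10% | 2 v 5 | 1 − 0.90² = 19.0% | 1 − 0.90⁵ = 41.0% | 2.16 |
| 10% | 3 v 5 | 1 − 0.90³ = 27.1% | 41.0% | 1.51 |
| 10% | 3 v 7 | 27.1% | 1 − 0.90⁷ = 52.2% | 1.93 |
| 15% | 3 v 5 | 1 − 0.85³ = 38.6% | 1 − 0.85⁵ = 55.6% | 1.44 |

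Over the whole grid the RR runs from 1.44 to 3.09, against the intervention.

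With a true 30% reduction per sample in the intervention arm and *p* = 10%, that arm still looks worse: 3 v 5 samples gives (1 − 0.93⁵)/(1 − 0.90³) = 30.4%/27.1% = 1.12, and 2 v 7 gives (1 − 0.93⁷)/(1 − 0.90²) = 39.8%/19.0% = 2.10.

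**2. Counting positive samples.** Assumed: scheduled samples are 10% positive; a share *s* of clinic samples is symptom-driven with positivity *q*; the intervention arm has 5 home and 2 clinic samples, the control arm 2 clinic samples. Clinic positivity is *c* = (1 − *s*) × 0.10 + *s* × *q*. The control arm shows *c*, and the intervention arm shows (5 × 0.10 + 2*c*)/7.

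- *s* = 10%, *q* = 30%: *c* = 12.0%; intervention (0.50 + 0.24)/7 = 10.6%; RR 0.88.
- *s* = 20%, *q* = 50%: *c* = 18.0%; intervention (0.50 + 0.36)/7 = 12.3%; RR 0.68.
- *s* = 30%, *q* = 50%: *c* = 22.0%; intervention (0.50 + 0.44)/7 = 13.4%; RR 0.61.

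Over *s* = 10% to 30% and *q* = 30% to 50% the RR runs from 0.61 to 0.88, in favour of the intervention. If *s* = 0 the RR is 1.00: on this unit it is the kind of visit that biases, not the number of samples.

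**3. Delivery sample only.** One sample per woman on the same schedule in both arms gives a no-effect RR of 1.00 on either unit.

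**The case against.** **The unit is not ever-positive.** The only prevalence definition in the Analytical plan, given for placental malaria, divides positive samples by all samples. Carried over to this endpoint, it would not rise mechanically with the number of visits. This stands, and it rules out one tempting inference: that the design must make the intervention look harmful. The per-sample reading can err the other way, and the text does not fix the unit for repeated samples.

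**The inputs are assumed.** This also stands. Positive correlation between a woman's samples would shrink the per-woman ratios; with complete dependence they fall to 1.00. The existence of a bias needs only unequal sampling, which the protocol does fix; its size cannot be read from the documents.

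**An unseen analysis plan may restrict the samples.** The text does not say that home and clinic samples are pooled, and the schedule figure is not shown. But a later plan cannot supply control samples that were never taken. It could only narrow the comparison, which is the change proposed here. Restricting it to ANC samples is not a full cure, since the intervention aims to change attendance. If return ANC visits bring only a rapid test on suspicion of malaria, as a narrow reading of At the antenatal clinic allows, controls have still fewer comparable samples.

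**SP markers.** A reader might infer that the marker comparison is biased in the same way. A profile is a proportion among positives, so more samples do not bias it by themselves, and delivery samples supply markers from both arms on equal terms. The concern is limited to a comparison that pools positives from all study samples, where the positives would differ in kind. No size was calculated for it.

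**Controls are not sampled solely at the clinic.** The text says mainly, and home deliveries are sampled in both arms.

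**Conclusion.** The point holds for the during-pregnancy part of the peripheral infection endpoint. As written, that contrast cannot be read as protective efficacy, because sampling differs by arm in number, timing and trigger. With no true effect the illustrative risk ratios are about 1.4 to 3.1 per woman and about 0.6 to 0.9 per sample. Both ranges rest on assumed counts and positivities, and the first also on independent samples.

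A reader might infer that the trial's main result, or the peripheral infection endpoint as a whole, is compromised. The documents do not support that. Placental malaria is assessed once, at delivery, in both arms; infection at delivery is sampled alike; and the other delivery outcomes and the sample size are untouched. This is a should-fix on a secondary endpoint.

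**What to change.** Amend Secondary endpoints and items (ii) and (v) of the Analytical plan:

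- Make the delivery sample the between-arm time point for peripheral infection, by microscopy and by PCR, and for SP-marker profiles.
- Show the enrolment sample by arm as baseline, read together with gestational age, because CHWs encourage earlier ANC attendance and may shift when that sample is taken.
- Report samples taken during pregnancy descriptively, by arm and by source (CHW visit or ANC visit), with the number of samples per woman, and not as protective efficacy.

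Cost: a change of wording, with no new data. One between-arm secondary contrast becomes descriptive, and the marker comparison rests on delivery positives alone, so on fewer samples. Recruitment was under way when the article was submitted, so the change should be made and dated before the arms are compared.

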### Timetable of event

The recruitment of study subjects will last for 18 months. The expected duration for each study subject is approximately 6 months - from enrolment during pregnancy up to time of delivery. It is expected that the total duration of the trial will be 24 months to allow the delivery of the last recruited pregnant woman.

### Ethical approval

Ethical approval by the Gambia Government/MRC laboratories Joint Ethics Committee was obtained on 25 June 2013 (ref SCC1336). Ethical approval by the Institutional Ethics Committee of Centre Muraz in Burkina Faso was obtained on 19 September 2013 (ref A20-2013/CE-CM). Ethical approval by the Comité National d’Ethique pour la Recherche en Santé in Benin was obtained on 9 December 2013 (N^o^_0126/MS /DC/SGM /DFR /CNERS/SA).

## Discussion

To reach successful global malaria control, there is an urgent need to access those at greatest risk of malaria infection. IPTp-SP if given at least twice after the first trimester has been shown to be effective in preventing malaria infection and its consequences during pregnancy. However, in the majority of sub-Saharan African countries, IPTp-SP coverage is low, with only 22% of pregnant women receiving IPTp-SP [16]. Systematic screening of pregnant women for malaria, and treating them if positive may further reduce the burden of malaria in pregnancy. In Ghana, an area of moderately high transmission, screening by RDT at scheduled ANC visits and treating positive women was as effective as IPTp-SP [29]. However, both interventions are currently being implemented through health facilities and thus the health system essentially waits for the women to attend a facility and does not tackle the issue of low or untimely (late in pregnancy) attendance. Further issues with delivery of these interventions include: unclear policy and guidance of IPTp-SP, stock outs at health facilities for both bed nets and SP, and poor quality of care. Low IPTp-SP coverage was also associated with poor education, poor knowledge of malaria, socio-economic status and age [30]. In rural areas, this is a major issue as pregnant women often have limited access to health facilities due to distance, poverty, low levels of education, strong traditional values, limited access to information and poor road infrastructure [31, 32]. Long distances can be an actual barrier for attending a health facility but they can also be a deterrent to seeking care [33].

In this study, it is proposed to add an “extension” strategy to the communities in rural areas to the standard IPTp-SP delivered through the health facilities and thus bring health services closer to where women live. The study will build on the use of CHWs who are already managing malaria cases within the framework of CCMm [18]. At this level, RDTs for the diagnosis of malaria are already being used or their implementation is planned. CCMm supported by RDT is at various stages of implementation; in The Gambia, the National Malaria Control Program is planning to introduce nationwide CCMm supported by RDT; in Burkina Faso, CCMm has been implemented and is currently managed by an international non-government organisation (Plan International) and four local non-government organisations under the supervision of the National Malaria Control Program; in Benin, CCMm is part of the National Malaria Policy, though it still needs to be scaled up nationwide.

The study will extend the CCMm which at present is primarily aimed at children under the age of 5 years to pregnant women. The aim is to improve both IPTp-SP coverage as CHWs encourage women to attend the ANC for the IPTp at the right time, allow systematic screening for malaria infection and provide an opportunity to treat malaria when the prophylactic effect of IPTp-SP has waned. The trial will also investigate the prevalence of SP resistance markers in the positive malaria samples obtained during the study as it could be hypothesized that the beneficial effects of the intervention might be more pronounced in areas with high SP resistance, because women could be more prone to placental malaria when IPTp-SP has a reduced effect and, although not yet observed in West Africa, extremely high levels of SP resistance markers in the parasite population may even lead to adverse effects of SP [34].

## Trial status

At time of submission of this paper, ethical approval has been obtained, and recruitment is ongoing in all three study sites.

## Abbreviations

AL: artemether-lumefantrine
ANC: antenatal clinic
CCMm: community case management of malaria
CHW: community health worker
CSST: community-scheduled screening and treatment
IPTp-SP: intermittent preventive treatment during pregnancy with sulfadoxine-pyrimethamine
PCR: polymerase chain reaction
RDT: rapid diagnostic test
SAE: serious adverse event.
